### Withdrawal of individual subjects

Subjects can leave the study at any time for any reason if they wish to do so without consequences. As this is an observational study, this will only have influence on the study related assessments. Individual subjects withdrawn from the study will not be replaced. In the sample size a dropout rate of 10% was calculated for.

### Data analysis

Data analysis will be carried out based on the intention-to-treat principle. Cross-over-cases (e.g. surgery after failed conservative treatment) will be analysed among the original treatment group. This will not cause methodological problems because it is two healthcare strategies that are being compared, as opposed to two specific treatments. The reasons for cross-over of patients will be studied and reported. Causes of death will be analysed and a potential relation to the diagnosis and the applied treatment will be studied.

As-treated analysis will additionally be carried out in a sensitivity analysis and prognostic factors for the likeliness of surgery after failed conservative treatment will be studied.

## Discussion

In this article the rationale and design of a prospective cohort study on surgical versus conservative treatment for odontoid fractures in the elderly is described. There is a lacuna in evidence-based knowledge and guidelines in treating this patient population. To the authors’ knowledge, only one prospective study on this subject has yet been published, involving 159 patients ≥65 years with type II fractures but focusing just on characteristics associated with treatment success or failure and not on describing fracture healing [14]. However, the INNOVATE Trial will specifically aim to evaluate the outcome separately for patients younger and older than 80 years. Moreover, not only fracture union, but also fracture stability will be evaluated in the INNOVATE trial, which will be correlated to clinical outcome. A combination of (relative) fracture stability and favourable clinical outcome might be a legitimate endpoint of treatment in elderly patients, although long term effects have to be investigated. The objective of this trial is to identify which treatment strategy is most favourable for elderly patients with acute type II and III odontoid fractures and to identify factors that predict the success of either one of the available treatment in individual patients. The results of this trial will yield valuable information enabling more rational decision making in the treatment of odontoid fracture in elderly patients.

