**Methods/Design:**

The trial is an observational study in which eleven centres in five European countries are involved. All patients admitted to one of these centres who meet the selection criteria (≥55 years, acute (<two weeks) type II/III odontoid fracture, no rheumatoid arthritis, no ankylosing spondylitis, no previous treatment for odontoid fracture) are asked to participate. The applied treatment is in accordance with usual care and chosen by the treating surgeon and patient. A cohort of 275 patients will be included. Clinical and radiological follow-up moments are scheduled at 6, 12, 26, 52 and 104 weeks, at which both surgeon and patient will complete Case Record Forms (CRFs). The primary outcome will be a combination of fracture healing and clinical outcome at 52 weeks. Osseous union and fracture stability will be assessed with CT-imaging and dynamic X-ray. Clinical outcome will be scored by the Neck Disability Index (NDI) and correlated to the imaging data. Additionally, predefined subgroup analysis will be carried out (i.e. for patient age and osteoporosis) and prognostic factors will be identified.

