Furthermore, the goal of treatment is still debatable. It is unknown whether or not non-union always leads to complaints in the patient. Consequently, debate remains as to whether the goal of treatment should be osseous union, fracture stability or a favourable clinical outcome. The measurement of these parameters is likewise not uniformly described. The available literature shows higher osseous union rates in surgically compared to conservatively treated patients (66–85% and 28–44%, respectively), but patient selection mechanisms may have profoundly interfered with these outcome percentages. The majority of patients achieved fracture stability regardless of the applied treatment (82-97% in surgically treated patients and 53-79% in conservatively treated patients). There are insufficient data available, especially from direct comparisons, to determine the difference in clinical outcome between surgical and conservative treatment strategies. There is no evidence that clinical outcome correlates better to fracture union than to fracture stability, or that the quality of union, whether it be osseous of fibrous, influences clinical outcome [12].

The goal of this study is to prospectively compare fracture union, fracture stability and NDI improvement at 52 weeks between surgical and conservative treatments in patients over 55 years of age with acute type II and III odontoid fractures. Predefined subgroup analysis may offer prognostic factors that can predict the success of either a surgical or conservative treatment. The influence of age (≥55-80 and ≥80 years) on treatment outcome will particularly be studied. The outcome of this study will yield valuable information enabling more rational decision making in treating the elderly patient population.

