### Sample size

Based on the recent literature review, the estimated possible difference in fracture union between the groups is 41% and in fracture stability this difference is 21% [12]. For both union and stability, however, a smaller difference of 20% would be clinically relevant and the study is powered to assess this difference. For the NDI, a 7.5 point difference (on a 50 point scale) is generally accepted as a minimal clinically important difference with a SD of approximately 10 in various psychometric studies [26-29]. Furthermore, it is expected that the number of patients that will be treated surgically will be twice the number of patients that are treated conservatively (2:1) [14]. Since three primary outcome hypotheses will be tested, the significance level (α) has to be divided by three. Based on the primary outcome parameters, the required sample size, assuming α = 0.05/3 = 0.0167 (two-sided) and β = 0.20 (80% power) and an expected drop out rate of 10%, is 275 for union, 198 for stability and 93 for the NDI. In conclusion, 275 patients will need to be recruited in order to give a reliable conclusion to the comparison of union, stability and clinical outcome between the surgically and conservatively treated groups.

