#### Multivariate analysis

Multivariate analyses will be carried out using regression models with dichotomised union, stability and NDI as dependent variables, and with the secondary outcome parameters as independent variables and covariates. Propensity score analysis will be used to generate a model to predict the treatment received with the baseline variables:

•Patient age (both dichotomised (≤80 and >80 years) and continuous)

•Fracture characteristics (type of fracture)

•Fracture displacement (in mm and direction)

•Severity of osteoporosis in C2

•Facet joint degeneration in C1-C2

•NDI

•MDI

•VAS neck pain

•SF-36

•EQ-5D

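### Age is a named effect-modification question, but the article states only separate evaluation below and above 80 and describes no treatment-by-age contrast

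*Protocol article*

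**What the plan says.** The Background names the aim: "The influence of age (≥55-80 and ≥80 years) on treatment outcome will particularly be studied". It adds that "Predefined subgroup analysis may offer prognostic factors that can predict the success of either a surgical or conservative treatment". The abstract (Methods/Design) promises that "predefined subgroup analysis will be carried out (i.e. for patient age and osteoporosis) and prognostic factors will be identified".

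The approach to age appears in the Discussion, where "the INNOVATE Trial will specifically aim to evaluate the outcome separately for patients younger and older than 80 years".

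Under Statistical analysis, the Univariate analysis section gives χ²-tests for union and stability and a t-test for NDI improvement, each comparing the two treatment groups. The Multivariate analysis section gives "regression models with dichotomised union, stability and NDI as dependent variables", "with the secondary outcome parameters as independent variables and covariates". Age enters that section only among the baseline variables of the propensity model: "Patient age (both dichotomised (≤80 and >80 years) and continuous". No treatment-by-age or treatment-by-osteoporosis term is described, and the Sample size section covers the overall comparison only.

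**The concern.** Whether the better strategy differs in the very old, and which factors predict success of one treatment rather than the other, are questions about effect modification. The quantity of interest is the difference between two treatment effects. Separate evaluation gives two effects, each less precise than the overall one, and neither estimates nor tests the difference between them. A prognostic factor found as a main effect shows who does well, not which treatment suits whom.

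The overall comparison has 80% power at the design effect, so each age stratum must have less. If the stratum results are compared by their significance, a common effect can easily be significant in one stratum and not in the other. If fewer than half the patients are over 80, the discordance leans towards a result in the younger group only. That would bear directly on whether to operate on the very old, which the Background presents as an open question.

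**Working it through.** **Inputs from the article (Sample size; Background).** α = 0.05/3 = 0.0167 two-sided, 80% power, 10% dropout, surgical to conservative 2:1, 275 recruited. Design differences: 20 points for union and for stability; 7.5 NDI points with SD 10. Literature: union 66-85% surgical and 28-44% conservative, estimated difference 41 points.

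**Assumptions.** The article gives neither the base rates behind its sample size nor the share of patients over 80. I vary the under-80 : over-80 split from 50:50 to 75:25 and assume 2:1 treatment in both strata.

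**The plan's own figures first.**
- NDI: (1 + 1/2) × [10 × (2.394 + 0.842)/7.5]² = 27.9, so 28 + 56 = 84. Then 84 × 1.1 = 92.4, which gives the stated 93 (84/0.9 gives 94).
- Union: 275 cannot be reproduced from stated inputs. Solving backwards at 2:1, 58% v 78% gives 246, and 246/0.9 gives 274. Other pairs also come close.
- Stability: 72% v 92% with continuity correction gives 180, then 200, against the stated 198.

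**Power within a stratum.** Evaluable: 275 × 0.9 = 247.5, taken as 247. With arms n₁ and n₂ = 2n₁ and pooled rate p̄:

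power = Φ{[|p₂ − p₁| − z·√(p̄(1−p̄)(1/n₁ + 1/n₂))] / √(p₁q₁/n₁ + p₂q₂/n₂)}

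P(exactly one stratum significant) = π₁(1 − π₂) + π₂(1 − π₁), where π₁ and π₂ are the two stratum powers.

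*Union 58% v 78%, split 50:50, α = 0.0167.* Each stratum has 41.2 v 82.3 and p̄ = 0.713. The two standard errors are 0.0863 and 0.0895. Power = Φ[(0.20 − 2.394 × 0.0863)/0.0895] = Φ(−0.07) = 0.47. Exactly one significant: 2 × 0.47 × 0.53 = 0.50.

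*Same rates, split 75:25.* Powers are 0.67 and 0.23. Exactly one significant: 0.67 × 0.77 + 0.23 × 0.33 = 0.59, of which 0.51 is the younger group only.

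**Probability that exactly one stratum is significant when the effect is the same in both**

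| Outcome and assumed rates | α = 0.0167 | α = 0.05 |
|---|---|---|
| Union, 20 points, 58% v 78% | 50-59% | 46-57% |
| Union, 20 points, 40% v 60% | 47-55% | 49-59% |
| Stability, 20 points, 72% v 92% | 43-58% | 30-46% |
| Union, 41 points, 44% v 85% | 2-17% | 1-8% |
| NDI, 7.5 points, SD 10 (50:50 and 67:33 only) | 12-22% | 5-11% |
| No effect | 3% | 10% |

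A third union pair, 62% v 82%, gives 44-60% across both α levels. Simulation (200,000 runs, 50:50 and 67:33) gave 46-55% for the two 20-point union pairs in the table. For NDI at 75:25 and α = 0.0167, the older stratum has 20.6 v 41.2 and SE = 10√(1/20.6 + 1/41.2) = 2.70, so power is Φ(7.5/2.70 − 2.394) = 0.65. With 0.99 in the younger group, exactly one is significant in about 35%. The NDI range therefore depends on the split.

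**The interaction test.** In the same simulations with a uniform effect, it was falsely significant in about 2% of trials at 0.0167 and 5-6% at 0.05.

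Its precision, with f the younger share: Var = (3/N)(p₁q₁ + p₂q₂/2)[1/f + 1/(1−f)]. At 40% v 60%, N = 247 and f = 0.5, this is (3/247)(0.24 + 0.12)(4) = 0.0175, so SE = 0.132. Power for a true 20-point interaction is Φ(0.20/0.132 − 2.394) = 19% at 0.0167, and 33% at 0.05. At 67:33 it is 17% and 30%. The 95% interval at 50:50 is about ±1.96 × 0.132 = ±26 points. For 80% power, about 1035-1280 evaluable patients would be needed at 0.0167, or 776-959 at 0.05 (over both union rate pairs in the table).

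**The case against.** The strongest reply is that this rests on what a condensed article leaves out. The full protocol and any SAP are not shown, subgroup analysis is called predefined, and the Multivariate analysis section is so brief that it does not even list treatment among the independent variables. A reader might infer that the trial has no interaction analysis. The documents support only that none is described. That part of the objection stands.

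A reader might also infer that the plan will declare age-dependence whenever one stratum is significant and the other is not. No section states that rule, and the Discussion sentence is equally compatible with stratum estimates and confidence intervals. That stands too: the probabilities above describe what separate testing would produce, not a decision rule the plan has adopted.

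Third, the base rates and age split are assumptions, and a conservative union rate of 58% lies above the 28-44% reported in the Background. This changes little for union at 20 points, because 40% v 60%, whose conservative rate is inside that range, gives 47-59%.

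What the objection does not remove is that the article states an approach as well as an aim, and the stated approach does not answer the stated question. Nothing else in it compares the two age groups' treatment effects.

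**Conclusion.** The point holds in a limited form. Age is a named effect-modification question, separate evaluation is the only approach stated, and that approach cannot show whether the effect differs by age.

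The size is conditional. For union at the 20-point design difference, a uniform effect would be significant in only one age group about half the time (roughly 46-59%). A reader might extend this to any uniform effect on any primary outcome, and the calculations do not support that. The range is about 30-58% for stability, 5-22% for NDI (splits of 50:50 to 67:33), 1-17% for union at 41 points, and 3-10% with no effect.

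These figures assume 247 evaluable patients, 2:1 treatment in each stratum, and the rates and splits listed. The overall primary comparisons are not affected; only the conclusions about age and osteoporosis are exposed.

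**What to change.** In the Multivariate analysis section:

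1. State that treatment is in each outcome model, and add a treatment-by-age interaction for each primary outcome. Use the 80-year split that the article names, with continuous age as a supplement. Settle to which group a patient aged exactly 80 belongs, because the Background and the Multivariate analysis section cut age differently.
2. Add a treatment-by-osteoporosis interaction for the other predefined subgroup, for example with the four grades as an ordered score.
3. State that any claim that the treatment effect differs will rest on the interaction estimate and its confidence interval. Name the scale for the binary outcomes. Present the under-80 and over-80 estimates as descriptive.
4. Label these analyses exploratory.

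Cost: no new data. Two interactions for each of three outcomes make six, plus the continuous-age supplement, and more if osteoporosis is treated as categorical. Power is low (about 17-33% for a true 20-point interaction on union) and the interval will be wide. The age conclusion will be more cautious, and a non-significant interaction must not be read as proof of a common effect.

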## Abbreviations

CRF: Case record form; CT: Computed tomography; NDI: Neck disability index; SIPS Group: Spine intervention prognostic study group; MDI: Myelopathy disability index; VAS: Visual analogue scale; SF-36: Short Form-36 Health Survey; EQ-5D: EuroQol 5 dimensions (generic measure of health); DS14: Type D Scale-14 (psychometric properties); IPQ-K: Illness perception questionnaire-K.
